## 2. Study 2: Follow-Up Of Non-Randomised Low Risk Subjects

### Study objectives

The primary objective of **Study 2 **is to determine the relationship between albumin excretion and cIMT both at baseline and after 3-4 years in subjects deemed to be at low risk on the basis of urinary albumin excretion when aged 11-16 years.

The secondary objective is to determine the relationship between albumin excretion and changes between baseline and 3-4 years in: 1) additional measures of subclinical atherosclerosis, such as endothelial function and arterial stiffness; 2) CVD risk markers: hsCRP and ADMA; 3) arterial BP, blood lipids and lipoproteins; 4) GFR as assessed by SDMA, creatinine and cystatin C levels; 5) long-term outcomes with regard to incidence of DN and CVD.

### Study endpoints

The primary endpoint is the relationship between ACR and cIMT and how this changes during puberty.

The secondary endpoints are: 1) changes in FMD, EndoPAT, PWV between baseline and the end of the study; 2) changes in arterial BP, lipids and other lipoproteins, CVD risk markers (hsCRP and ADMA), assessed annually; 3) changes in measures of GFR (plasma SDMA, creatinine and cystatin C), assessed annually; 4) changes in retinopathy scores and in the retinal microvasculature (arteriolar or venular dilation, vascular fractal dimension, branching and tortuosity), assessed annually.

### Method/Design

#### Study design

This will be an open observational study of low-risk subjects in the UK. In the UK, 400 subjects not recruited into the interventional study (from the medium and low tertiles of ACR) will be assessed at baseline with measurement of cIMT (and FMD, EndoPAT and PWV where facilities allow), BP, lipids, HbA1c, and CVD markers and renal function. Copies of the most recent digitalized retinal photographs, performed as part of the annual routine screening, will also be collected and retained for centralized assessments. These subjects, together with 200 high risk individuals in the UK from the RCT will form the cohort of 600 subjects to enable the study of the relationship between markers of sub-clinical atherosclerosis (cIMT, endothelial function and arterial stiffness), and albumin excretion and its modification by cardiovascular risk factors, renal function and diabetes control. 200 of the low risk subjects will be re-assessed annually and 3-4 years after initial screening. The findings will be compared to treated subjects from the interventional trial including 100 high risk subjects randomized to placebo arm. The aim is to provide additional data concerning the natural history of renal, cardiac and retinal measures in subjects deemed to be at different levels of risk.

#### Study population

##### • Definition of low-risk subjects

As in the RCT, during the screening phase of the study two ACR measures, each based on three early morning urine samples, are to be provided by a subject. These will be averaged on the log ACR scale and the subject's average residual will be calculated using gender, age, age at diagnosis and duration of diabetes, as well as the coefficients from the ORPS linear regression model. If the subject's residual lies below log 1.2 the patient will lie in the medium or lower tertile indicating low risk and eligibility for the non-randomized study.

• Inclusion and exclusion criteria

*Inclusion criteria*

1) Age 11 to 16 years; 2) T1D diagnosed for more than 1 year or C-peptide negative; 3) Centralized assessment of ACR based on six early morning urines deemed to be in middle or lower tertiles for risk after adjustment for age, gender, age at diagnosis and duration of disease.

*Exclusion Criteria*

The presence of any of the following will preclude patient participation: 1) Non T1D, i.e. type 2 diabetes, insulin dependent diabetes related to monogenic disease, secondary diabetes; 2) ACR based on six early morning urines deemed to be at high risk for subsequent development of CVD or DN; 3) Severe hyperlipidaemia and family history data to support diagnosis of familial hypercholesterolaemia; 4) Established hypertension unrelated to DN; 5) Prior exposure to the investigational products, statins and ACEI; 6) Other co-morbidities considered unsuitable by the investigator (excluding treated hypothyroidism and celiac disease); 7) Proliferative retinopathy.

##### • Sample size determination and power calculations

Based on a previous pediatric cohort of 45 patients with T1D with mean cIMT of 0.58 (SD 0.05), a sample size of 600 subjects at baseline (200 subjects evaluated per tertile of ACR) would allow mean cIMT in this population to be estimated precisely with 95% confidence interval of ± 0.004 mm and would provide 83% power to detect an unadjusted correlation of ≥ 0.12 between cIMT and ACR (α = 5%). This will allow sensitive detection of the association between ACR and cIMT after adjustment for potential confounders (such as age, gender, blood pressure, lipids, inflammation and HbA1c) using multiple linear regression.

For the analysis including data from baseline and at the end of the study, 300 subjects (100 high risk subjects from the RCT plus 100 low risk subjects from the middle and lower tertiles of ACR), the study will provide 80% power to detect correlation coefficients, such as between cIMT and ACR ≥ 0.16 (α = 5%). Assuming the same standard deviation of 0.044, analysis of the trend in cIMT across all three tertiles of ACR allows a range of ≥ 0.035 mm in mean cIMT to be detected across tertiles, and ≥ 0.022 mm between two tertiles. The analysis will include a regression model incorporating the 600 cIMT measures from subjects where cIMT was measured at both baseline and follow-up, to estimate the shape of progression of cIMT by gender and age over time and in relation to puberty and other potentially predictive characteristics.

For FMD, an estimate across recent studies of the SD of change from baseline is 2.5. 70 subjects will give >90% power to detect a 1% difference in FMD between baseline and final assessment at a 5% level of significance. For PWV, an estimate across recent studies of the SD of change from baseline is 1.5. 95 subjects will give 90% power to detect a 0.5 m/sec difference in PWV between baseline and final assessment at a 5% level of significance.

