##### Baseline assessment

Once consent has been obtained, baseline assessments will be undertaken within 3 months of recruitment. These assessments will include: cIMT (and FMD, EndoPAT and PWV where facilities allow), blood samples for lipids and lipoproteins, CVD risk markers, SDMA, creatinine, cystatin C, three early morning urines for ACR and collection of anonymised digital copies of the most recent retinal photographs, performed as part of the annual routine screening, for centralized assessments. These subjects will also be asked to complete annual questionnaires regarding quality of life and to provide data for economic assessments during the study period. It is anticipated that 200 of these subjects will agree to the assessment of ACR (3 urines), blood tests and cardiovascular assessments and to retain copies of their retinal photographs for centralized assessment at the end of the study period. This will provide additional data concerning the natural history of these markers of complications risk. These 200 subjects will be asked to consent to long-term follow up and re-assessment five years after the end of the study period.

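### Study 2: the 0.035 mm detectable range for the three-tertile cIMT trend is too large for the stated SD and group sizes; the error is conservative

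*Protocol article*

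**What the plan says.** The follow-up figures are in one paragraph of the protocol article, under Study 2, Sample size determination and power calculations.

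- **Cohort.** "For the analysis including data from baseline and at the end of the study, 300 subjects", which the parenthesis breaks down as "100 high risk subjects from the RCT plus 100 low risk subjects from the middle and lower tertiles of ACR". For this cohort the paragraph claims 80% power to detect a correlation of 0.16 or more between measures such as cIMT and ACR at the 5% level.
- **cIMT differences.** Reusing the SD of 0.044, the trend analysis over all three tertiles "allows a range of ≥ 0.035 mm in mean cIMT to be detected across tertiles". The figure given for two tertiles is 0.022 mm. Neither figure carries its own significance level or power.
- **Longitudinal model.** A "regression model incorporating the 600 cIMT measures from subjects where cIMT was measured at both baseline and follow-up".

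Two other places give the number of low-risk subjects followed up. Study 2, Study design, says "200 of the low risk subjects will be re-assessed annually and 3-4 years after initial screening" and compares them with treated trial subjects, "including 100 high risk subjects randomized to placebo arm". Study 2, Baseline assessment, says "It is anticipated that 200 of these subjects will agree to the assessment of ACR (3 urines), blood tests and cardiovascular assessments" at the end of the study.

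**The concern.** The trend across three tertiles is presented as needing a larger difference (0.035 mm) than a comparison of two of those tertiles (0.022 mm). With equal groups and a common SD this cannot be so. The linear trend estimates the top-minus-bottom range with the same precision as a direct comparison of the extreme tertiles, so on the same significance level and power the two detectable differences should agree.

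The relationship between ACR and cIMT is the primary endpoint of Study 2, and these figures are part of the justification for following 300 subjects. A reader who takes 0.035 mm at face value will think the trend analysis much blunter than it is. Because the significance level and power are left unstated, that reader also cannot tell which basis either cIMT figure uses.

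The breakdown of the 300 is a smaller matter. Its listed components do not add up as printed, and it is the sentence that defines the longitudinal sample.

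**Working it through.** **Inputs**

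- SD 0.044 mm: Study 2 sample size section, carried over from Study 1.
- 300 subjects at follow-up, taken as 100 per ACR tertile: Study 2 sample size section, read with Study design and Baseline assessment.
- Two-sided tests, 5% for primary and 1% for secondary outcomes: Statistical analysis.
- In Study 1, 0.022 mm is given 82% power for single-arm comparisons of 100 against 100, with secondary outcomes at the 1% level: Study 1, Power calculations for secondary endpoints.

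**1. Size of the follow-up cohort**

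Study design gives 200 low-risk plus 100 placebo subjects = 300. Baseline assessment also expects 200 low-risk subjects at the end. In the longitudinal model, 600 cIMT measures ÷ 2 time points = 300 subjects. All agree with the stated 300, so the parenthesis lacks a word such as *each*.

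**2. Correlation power (reproduces)**

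Fisher z: power = Φ(√(n − 3) × atanh(r) − 1.96).

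For n = 300 and r = 0.16: √297 × 0.1614 − 1.96 = 2.781 − 1.960 = 0.821, and Φ(0.821) = 79.4%. The plan says 80%.

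The baseline claims in the same section reproduce too. For n = 600 and r = 0.12 the power is 83.8% (stated 83%). The confidence half-width is 1.96 × 0.05/√600 = 0.0040 mm (stated 0.004).

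**3. Two-tertile figure (reproduces on the Study 1 basis)**

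SE = 0.044 × √(2/100) = 0.00622 mm, and 0.022/0.00622 = 3.536.

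- At 1%: Φ(3.536 − 2.576) = 83.1%, in line with the 82% in Study 1.
- At 5%: Φ(3.536 − 1.960) = 94.2%.

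The 0.022 mm therefore fits a 1% level with about 82% power.

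**4. Trend figure (does not reproduce)**

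Score the tertiles 0, 1, 2. With 100 in each, Sxx = 100 × (1 + 0 + 1) = 200. The range is twice the slope, so

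SE(range) = 2 × 0.044/√200 = 0.00622 mm,

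which is identical to step 3. The detectable range is (z for significance + z for power) × 0.00622:

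| Significance, power | Detectable range |
|---|---|
| 5%, 80% | 2.802 × 0.00622 = 0.0174 mm |
| 5%, 90% | 0.0202 mm |
| 1%, 82% | 3.491 × 0.00622 = 0.0217 mm |
| 1%, 93% | 0.0252 mm |

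Replacing the linear trend by a two-degree-of-freedom analysis of variance with evenly spaced means gives 0.0194 mm (5%, 80%) to 0.0274 mm (1%, 93%). None of these reaches 0.035 mm.

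**5. What 0.035 mm would mean**

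0.035/0.00622 = 5.625. Power is Φ(5.625 − 1.960) = 99.99% at 5% and Φ(5.625 − 2.576) = 99.89% at 1%. Detecting 0.035 mm between the extreme tertiles would take only 25 subjects per tertile at 5%/80%, or 39 at 1%/82%, against the 100 planned.

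**The case against.** **The error is harmless.** A range of 0.035 mm or more can indeed be detected, with power near 100%, so the sentence is not false as a lower assurance. No analysis is underpowered and no sample size would change. This stands, and it limits the point to a wrong stated figure. It does not remove it, because the number is given as the threshold of detectability and conflicts with the figure beside it.

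**The basis is unstated, so some choice might give 0.035.** Values near it do arise if the SD is inflated: 0.044 × √2 at 1% and 93% power gives 0.0357 mm. But the paragraph says the SD is the same 0.044. The figure is also close to twice the 5%/80% value (2 × 0.01743 = 0.0349), so a doubling slip is possible, but that is inference. On the 1%/82% basis the ratio is about 1.6 (0.035/0.0217), so the size of the overstatement depends on the basis chosen.

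**A stronger reading: the follow-up is underpowered.** A reader might infer this from the parenthesis, whose components add to 200. The documents do not support it. The stated total is 300, the Study design and Baseline assessment sections and the count of 600 measures all agree with it, and the claimed power reproduces at that number.

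**A second stronger reading: only UK placebo subjects count.** A reader might also infer that too few placebo subjects are available, because "200 high risk individuals in the UK from the RCT will form the cohort of 600 subjects". That sentence describes the baseline cohort. The sentence on the follow-up comparison names no country, 100 is the planned placebo arm of the whole trial (Study 1 power calculations), and cIMT is measured at baseline and end of study in all three countries (Cardiovascular assessments).

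**Conclusion.** The 0.035 mm figure is wrong as written. With SD 0.044 mm and 100 subjects per tertile, the detectable range for the linear trend is 0.0174 mm at 5% and 80% power, or about 0.022 mm at 1% and 82%. The stated value is therefore about 2.0 or 1.6 times too large, depending on the basis. The error is conservative: it understates what the Study 2 follow-up analysis can detect, leaves every sample size unchanged and does not touch the randomized trial.

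The breakdown of the 300 is a wording slip. The 80% power for a correlation of 0.16 stands.

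The conclusion rests on equal tertiles of 100, a common SD of 0.044 mm as the plan states, equally spaced tertile scores and two-sided tests.

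**What to change.** In Study 2, Sample size determination and power calculations:

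1. Replace 0.035 mm by the recalculated range, and state one significance level and power for both cIMT figures. Either 0.0174 mm for both (5%, 80% power) or about 0.022 mm for both (1%, 82% power) is consistent. The first matches the basis of the correlation claim in the same paragraph; the second matches the Study 1 basis for 0.022 mm.
2. Reword the breakdown of the 300 as 100 high-risk subjects from the trial plus 100 from each of the middle and lower ACR tertiles.

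Leave the 80% power for a correlation of 0.16 as it is. The cost is a change of wording and one restated figure, with no extra subjects or assessments.

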#### Study Procedures (Figure 1)

##### Recruitment

Eligible subjects and their families will be approached by the research nurse and the local PI and they will be provided with a verbal explanation of the study, and written information sheets. Once they have been given sufficient time to consider their participation in the trial, the parents will be asked to provide written informed consent and children to provide evidence of their assent to the study procedures.

##### Baseline assessment

Once consent has been obtained, baseline assessments will be undertaken within 3 months of recruitment. These assessments will include: cIMT (and FMD, EndoPAT and PWV where facilities allow), blood samples for lipids and lipoproteins, CVD risk markers, SDMA, creatinine, cystatin C, three early morning urines for ACR and collection of anonymised digital copies of the most recent retinal photographs, performed as part of the annual routine screening, for centralized assessments. These subjects will also be asked to complete annual questionnaires regarding quality of life and to provide data for economic assessments during the study period. It is anticipated that 200 of these subjects will agree to the assessment of ACR (3 urines), blood tests and cardiovascular assessments and to retain copies of their retinal photographs for centralized assessment at the end of the study period. This will provide additional data concerning the natural history of these markers of complications risk. These 200 subjects will be asked to consent to long-term follow up and re-assessment five years after the end of the study period.

##### Follow-up assessments

As routine, subjects will be seen quarterly in clinics with local assessment of HbA1c to facilitate appropriate medical care and where appropriate intensification of insulin therapy. Height, weight, waist circumference and arterial BP will also be assessed at each visit.

Every 6 months, three early morning urine samples will be collected for centralized analysis of the ACR. Pubertal stage and smoking status will also be assessed.

Annually, blood samples will be taken for lipids and lipoproteins, CVD risk markers, SDMA, creatinine, cystatin C and subjects will also be asked to fill in a questionnaire to provide control data for quality of life and health economics assessment of the intervention cohort. Anonymised digital copies of the most recent retinal photographs, performed as part of the annual routine screening, will be collected and retained for centralized assessment.

#### Long-term follow up of screened and intervention cohort (Study 1 and Study 2)

The primary and secondary outcomes of the study are robust, but they are surrogates for long-term DN and CVD risk. It is therefore essential that planned follow-up of the cohort is undertaken. In the UK all of the subjects, both randomized and non-randomized controls will be flagged by the UK Office for National Statistics (ONS) in order to track them through the UK National Health Service database and to permit tracing and outcome assessment by local consultants and to receive notifications of deaths. We will undertake similar tracking of subjects in Canada and Australia using national health numbers and diabetes registers.

In addition we plan formal re-assessment of all randomized (400) and non-randomized subjects (UK 200) five years after the end of the study, subject to successful completion of the study and securing further funding. This assessment would include cIMT (and FMD, EndoPAT and PWV where facilities allow) and markers of CVD risk combined with a comprehensive assessment of microvascular complications including urinary albumin excretion, GFR and retinal photographs. To facilitate this long-term follow-up we will endeavor to keep in touch with the cohort through annual newsletters.

## 3. Common Methods For Study 1 And Study 2

### Data management

At screening, all subjects are given a unique identifying number which will be translated into a barcode used for all subsequent correspondence, transfer of samples and data input to the centralized database. Study databases are developed "in house" and incorporate quality control (QC) checks to ensure accurate data entry data. Standardized CRFs have been developed for use in all centers. Results from the Central Laboratory for screened subjects will be available on a secure website in order to identify those eligible for recruitment and randomization.

Data from the CRFs will be entered onto a secure locally held database at each center with anonymised data regularly sent to the central database held at the Clinical Trials Unit in Cambridge. Off line checks will be run on data received to identify missing or inaccurate data and queries will be fed back to centers using existing SOPs. A random 10% of CRFs from each center will be double data entered by staff in Cambridge to provide an additional QA check.

### Laboratories

The WellChild laboratory at The Evelina Children's Hospital, London will undertake centralized assessments of all urinary screening samples, 6 monthly study urine samples and bloods for HbA1c, creatinine, SDMA, cystatin C, fasting lipids, lipoproteins, ADMA, and hsCRP. Urine albumin will be measured using laser immunonephelometry (Dade Behring) and for concentrations <2.1 mg/l by an enzyme linked immunoabsorbent assay (ELISA). Urine creatinine will be measured using a chromatographic stable isotope dilution electrospray mass spectrometry-mass spectrometry (MSMS) method. HbA1c % will be measured in filter paper blood spots, after endoproteinase Glu-C digestion, using an MSMS reference method measuring the -N-terminal hexapeptides of HbA1c and HbA0. GFR will be monitored using plasma creatinine measured by a NIST traceable MSMS method and estimated GFR (eGFR) calculated from the formula: eGFR (ml/min/1.73 m^2^) = 42*height (cm)/plasma creatinine (μmol/l). GFR will also be monitored using plasma SDMA, measured by MSMS, and cystatin C, measured by laser immunonephelometry (Dade Behring); both GFR markers are independent of body size [82-84].

CVD biomarkers will include fasting lipids and lipoproteins, measured using routinely available methods, hsCRP by laser immunonephelometry (Dade Behring), and ADMA by MSMS. Serum and plasma will be stored at -80°C for future analysis of any compelling biomarkers. Local site-specific laboratories will analyze toxicology data (U&E, ALT) and pregnancy tests and details of local methods, normal ranges, QC and QA will be obtained during site set up visits and confirmed during monitoring visits. 3-monthly HbA1c will be also assessed in local laboratories, using DCCT aligned methods.

### Cardiovascular assessments

cIMT will be assessed at baseline and the end of the study in designated centers in the UK, Australia and Canada, through collaborative agreements. Where facilities and training allow, centers will also provide endothelial function assessment (by FMD and EndoPAT) and arterial stiffness assessment (by PWV) at baseline and at the end of the study.

cIMT will be quoted as end-diastolic mean-mean and end-diastolic mean-max. The maximum IMT measurement of a segment of arterial wall will be defined as the single point along an approximate one-centimeter length in which the lumen-intima and media-adventitia interfaces are separated by the greatest distance. Several maximum IMT measurements will be averaged to produce the mean-max IMT. The mean IMT measurement will be defined as the mean-mean of multiple single point IMT measurements across an approximate one centimeter segment of arterial wall. All IMT measurements will be made during end-diastole. One arterial wall segment will be imaged, this will be the common carotid 1 cm proximal to the dilatation of the bifurcation. During each ultrasound examination, the right and left common carotid arteries will be visualized and ultrasound images recorded at a single fixed interrogation angle. The head will be rotated to 45 degrees from the midpoint and the carotid artery scanned in the ear-ear plain. Optimal images will be triggered on the R-wave of the ECG and recorded in DICOM format as still images or as a cine loop onto CD for later offline analysis in the core laboratory. Arterial diameter measurements will also be recorded in order to calculate carotid distensibility.

FMD will be measured using high resolution ultrasound to image the brachial artery in the mid upper arm, proximal to a blood pressure cuff placed just below the antecubital fossa. During each ultrasound examination, the brachial artery will be scanned in longitudinal section and digitized ECG-gated end-diastolic images will be acquired. A hard copy of the B-mode brachial artery image will be stored. Diameter will be determined using an automatic edge-detection algorithm and blood flow measured from the velocity-time integral of the Doppler signal. Reactive hyperemia will be stimulated by inflation of a blood pressure cuff to suprasystolic pressure for 5 minutes, followed by deflation.

The EndoPAT system (endothelium pulse amplitude tonometry) will be used to give a measure of Reactive Hyperemic Index (RHI), a measure of endothelial function designed to be used in conjunction with FMD measurement of reactive hyperemia. The EndoPAT probe is a finger plethysmograph. One probe, formed as a thimble, is placed on each index finger. This probe causes a harmless occlusion of the finger and gives a uniform, near-diastolic external pressure over the distal index finger. The probes will be inflated for five minutes to record a baseline amplitude before the FMD cuff occlusion of the forearm is achieved. The FMD cuff will be inflated for five minutes and then will be deflated. During this time the probes on the index fingers remain inflated and will continue to remain inflated for a further five minutes after cuff deflation. RHI is calculated by integral software.

PWV will be calculated, using measurements obtained by the SphygmoCor system, from pulse pressure waveforms obtained from the carotid, radial and femoral arteries. A pressure tonometer will be placed at the site of each artery for a few seconds until a pressure waveform is recorded and the distance between the carotid-radial and carotid-femoral pulse points will be measured. Integral software calculates the pulse time delay between the points and uses this to give a PWV measurement. All sonographers participating in the cIMT measures will undertake specific training directed by the core laboratory in London (UK).

